### Randomisation and blinding

Randomisation is performed after the baseline assessment. Randomisation is stratified by severity of alcohol dependence (< = 30 and > 30), as measured by the Severity of Alcohol Dependence Questionnaire (SADQ), and by site. The University of York Trials Unit will perform remote randomisation. Confirmation of eligibility, consent, and baseline data will be obtained prior to randomisation. Research workers conducting follow up assessments are blind to the allocated intervention. All possible attempts at maintaining blinding will be pursued.

### Sample size and power calculation

As this study is the first to examine the effect size of ACT in alcohol dependence, there is no specific study on which to base the power calculation. In terms of alcohol consumption a proportional difference between the groups of 30% would be considered a clinically important difference. This equates to an effect size difference of 0.70 similar to the effect sizes found in Patterson et al study [38] and the Cochrane meta-analysis of ACT [19]. As a pilot study we have employed an alpha of 0.2 and power of 80%, a sample of 35 in each group followed-up at 12 months would allow us to detect an effect size of the order of 0.5, a more conservative estimate of effect than seen in similar studies. Allowing a loss to follow-up of 25% would suggest we require 45 in each group, a total of 90 participants. This number would allow us to estimate the potential effect, within 80% confidence intervals in order to enable more formal sample size calculations for a definitive study.

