**Methods/Design:**

In this single blind exploratory randomised controlled trial, a total of 90 alcohol dependent participants will be recruited from community addiction services. After completing a baseline assessment, they will be assigned to one of two conditions: (1) ACT plus care as usual, or (2) care as usual. Those allocated to the ACT plus care as usual will receive the same treatment that is routinely provided by services, plus a trained key worker who will provide ACT. ACT comprises intensive and assertive contact at least once a week, over 50% of contacts in the participant's home or local community, and comprehensive case management across social and health care, for a period of one year. All participants will be followed up at 6 months and 12 months to assess outcome post randomisation. The primary outcome measures will be alcohol consumption: mean drinks per drinking day and percentage of days abstinent measured by the Time Line Follow Back interview. Secondary outcome measures will include severity of alcohol dependence, alcohol related problems, motivation to change, social network involvement, quality of life, therapeutic relationship and service use. Other outcome variables are treatment engagement including completion of assessment, detoxification and aftercare.

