### Statistical analysis

The main hypothesis, stated as a null hypothesis, is that CAU augmented with ACT is no more effective than CAU in reducing alcohol consumption 12 months after randomisation. The primary outcome measures will be alcohol consumption: mean drinks per drinking day and percentage of days abstinent at 12 months measured using the Timeline Followback interview. The primary analysis will be intention-to-treat in which participants will be analysed as part of their allocated group irrespective of the treatment received; this provides the most rigorous estimate of effectiveness. The primary outcome measure will be analysed using an analysis of covariance approach adjusting for known confounding variables such as baseline mean drinks per drinking day, age and gender. If the assumptions underlying ANCOVA are not met transformations will be undertaken and if transformations are not viable alternative non-parametric approaches will be used. In order to explore the impact of missing data on the primary outcome measure we will employ multiple imputation techniques and conduct sensitivity analyses to measure any effect of missing data on reported outcomes.

Continuous secondary measures will be analysed in a similar manner. Categorical variables will be analysed using chi-squared statistics and binary outcomes analysed using logistic regression controlling for known confounding variables. Estimates and the 80% confidence intervals will be presented. In addition intra-class correlation coefficients relating to therapists will be calculated and estimates of recruitment, engagement in treatment, retention will be assessed to inform any future study.

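### The figures of 35 per group followed up, 25% loss and 45 per group recruited do not agree: 45 less 25% leaves 33.75, a small slip that one sentence corrects at N = 90

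*Protocol article*

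**What the plan says.** The section 'Sample size and power calculation' of the protocol article sets "an alpha of 0.2 and power of 80" per cent. On that basis it says that "a sample of 35 in each group followed-up at 12 months would allow us to detect an effect size of the order of 0.5". It then adds an allowance for attrition: "Allowing a loss to follow-up of 25% would suggest we require 45 in each group, a total of 90 participants". The Abstract repeats the total: "a total of 90 alcohol dependent participants will be recruited from community addiction services".

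The same section puts the clinically important effect at 0.70 and calls 0.5 a more conservative value. It gives no formula for the attrition allowance and does not say whether alpha is one-sided or two-sided. Under 'Statistical analysis' the article says "Estimates and the 80% confidence intervals will be presented".

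**The concern.** Two consecutive sentences give the number to be followed up, the expected loss and the number to be recruited. Any two of these fix the third, and the printed three do not agree. This is a conflict between stated numbers, not a detail that a condensed article would leave to a fuller document.

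Two things are at stake. First, a reader cannot tell whether the trial plans for 35 per group or for about 34. Second, the trial is meant to inform a definitive study, and retention is one of the quantities it will estimate. Observed retention will be compared with a planning figure, and the article supports two of them: 25% as printed and 22% as implied by the step from 45 to 35.

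**Working it through.** **Inputs from 'Sample size and power calculation':** alpha 0.2; power 80%; 35 per group followed up; detectable standardised effect about 0.5; loss 25%; 45 per group and 90 in total recruited; clinically important effect 0.70.

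**Assumptions:** two-sided alpha, equal groups and an unadjusted comparison of two means. Two-sided is the reading that fits. It matches the 80% confidence intervals, and a one-sided alpha of 0.2 would need only 23 per group for an effect of 0.5, far from 35.

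**Step 1: the 35 per group.** The normal-approximation formula is n = 2(z₁₋α/₂ + z₁₋β)²/d². With 1.2816, 0.8416 and d = 0.5, n = 2(2.1232)²/0.25 = 36.06. Read the other way, with n = 35 the effect detectable with 80% power is 2.1232 x √(2/35) = 0.508 (0.510 with the t distribution). The printed 35 is therefore reproduced at the precision the article claims.

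**Step 2: the allowance for loss.**
- Retained from 45 at 25% loss: 45 x 0.75 = 33.75 per group, or 67.5 in total against the 70 intended.
- Recruitment needed to retain 35: 35/0.75 = 46.67, so 47 per group and 94 in total.
- Loss implied by 45 and 35: 1 − 35/45 = 22.2%.
- Multiplying by 1.25 instead of dividing by 0.75: 35 x 1.25 = 43.75, so 44 per group. This does not give 45 either.

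**Step 3: the consequence.** Two-sided alpha 0.2, unadjusted:

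| Per group analysed | Power at 0.5 (normal) | Power at 0.5 (t) | Effect at 80% power (normal) | Effect at 80% power (t) |
|---|---|---|---|---|
| 35 | 79.1% | 78.8% | 0.508 | 0.510 |
| 33.75 | 78.0% | 77.7% | 0.517 | 0.520 |

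The slip costs about 1.1 percentage points of power at 0.5 and moves the detectable effect by about 0.01. At an effect of 0.70, power with 33.75 per group is about 94% (94.5% by the normal approximation). Confidence intervals widen by a factor of √(35/33.75) = 1.018, about 2%.

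**The case against.** A reader might infer that the trial does not deliver its stated power. The article does not support that. It does not claim 80% power at exactly 0.5. It says only that the sample "would allow us to detect an effect size of the order of 0.5". An effect of 0.52 fits that wording, so 80% power, an effect of about 0.5, 25% loss and N = 90 hold together at the precision given. Only the intermediate figure of 35 breaks. For the same reason, it would be wrong to press the difference between 35 and 36.06, or to ask for a larger total so as to reach a full 80% at exactly 0.5.

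Further points on the same side also carry weight:
- The planned analysis is ANCOVA, which can gain precision over the t-test used here. The article gives no correlation between baseline and outcome. If the residual variance falls by a factor 1 − r², then r² = 1 − (0.5/0.520)² = 0.075, so r of about 0.27 would bring 33.75 per group to 80% power at 0.5. With r = 0 the figures above stand.
- The trial is exploratory and the number is justified mainly by estimation. A 2% change in interval width is immaterial.
- The 25% is itself a planning guess, and the article words the step to 45 loosely.

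All of this limits the consequence. None of it makes 45 less 25% equal to 35, whichever test, sidedness or covariate adjustment is used.

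**Conclusion.** The inconsistency is certain, because it rests only on printed figures: with 45 recruited, 25% loss leaves 33.75 per group, and 35 are retained only if loss is no more than 22%. Its effect on the design is minor. Given two-sided alpha 0.2 and an unadjusted t-test, about 34 per group gives 80% power for an effect of about 0.52 and about 78% power at 0.5, before any gain from covariate adjustment. The total of 90 remains adequate for what the article claims. This is a low-severity correction to a sample-size statement, not a finding that the trial is too small.

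**What to change.** Keep N = 90 and change one sentence in 'Sample size and power calculation', in one of two ways:

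- state that 45 per group with 25% loss leaves about 34 per group at 12 months, which gives 80% power at alpha 0.2 for an effect of about 0.52; or
- state that 45 per group allows for 22% loss to follow-up while retaining 35 per group.

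The first is preferable if 25% is the loss the investigators expect, because it keeps that figure as the benchmark for judging retention. Either change costs one sentence and makes the stated detectable effect or the tolerated loss slightly less favourable. It needs no extra participants, and the total in the Abstract and the participant flow diagram stays as it is.

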### Statistical analysis

The main hypothesis, stated as a null hypothesis, is that CAU augmented with ACT is no more effective than CAU in reducing alcohol consumption 12 months after randomisation. The primary outcome measures will be alcohol consumption: mean drinks per drinking day and percentage of days abstinent at 12 months measured using the Timeline Followback interview. The primary analysis will be intention-to-treat in which participants will be analysed as part of their allocated group irrespective of the treatment received; this provides the most rigorous estimate of effectiveness. The primary outcome measure will be analysed using an analysis of covariance approach adjusting for known confounding variables such as baseline mean drinks per drinking day, age and gender. If the assumptions underlying ANCOVA are not met transformations will be undertaken and if transformations are not viable alternative non-parametric approaches will be used. In order to explore the impact of missing data on the primary outcome measure we will employ multiple imputation techniques and conduct sensitivity analyses to measure any effect of missing data on reported outcomes.

Continuous secondary measures will be analysed in a similar manner. Categorical variables will be analysed using chi-squared statistics and binary outcomes analysed using logistic regression controlling for known confounding variables. Estimates and the 80% confidence intervals will be presented. In addition intra-class correlation coefficients relating to therapists will be calculated and estimates of recruitment, engagement in treatment, retention will be assessed to inform any future study.

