### Assessments

#### Baseline assessments

(i) Socio-demographic details - age, sex, ethnicity, marital status, living arrangement, children, living arrangements of children, education

(ii) Drinking in the previous 90 days - Timeline Followback form 90I [30]

(iii) History of drug use - Timeline Followback

(iv) Alcohol related problems - Alcohol Problems Questionnaire [31]

(v) Severity of alcohol dependence -Severity of Alcohol Dependence Questionnaire [32]

(vi) Health utility - EQ-5D [33]

(vii) Health Related Quality of life - SF-12 [34]

(viii) Motivation to change - Readiness to Change Treatment version [35]

(ix) Social network involvement - Important People and Activities Inventory [36]

(x) Health service utilisation - York Service Use Questionnaire

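### The only baseline drinking covariate named fits one of the two primary outcomes; percentage days abstinent should be adjusted for its own baseline, and the stratification factors added

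*Protocol article*

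**What the plan says.** All of the following is in the protocol article. Under Statistical analysis, the primary outcomes are "mean drinks per drinking day and percentage of days abstinent at 12 months measured using the Timeline Followback interview". The model is then described in the singular, as if for one primary measure: "analysis of covariance approach adjusting for known confounding variables such as baseline mean drinks per drinking day". The other two covariates named are gender and age. No other baseline drinking measure appears in that section. For the secondary scales the rule is "Continuous secondary measures will be analysed in a similar manner", with no covariate list.

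Baseline assessments lists "Drinking in the previous 90 days - Timeline Followback form 90I", and Follow up assessments lists the same form, so days abstinent can be derived at both times. The SADQ, Alcohol Problems Questionnaire, EQ-5D, SF-12, readiness to change and social network measures are also taken at baseline and follow-up. The therapeutic relationship scale (STAR) is taken at follow-up only.

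Randomisation and blinding stratifies allocation by site and by SADQ score (30 or below, above 30). Neither factor is among the covariates named for the analysis.

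**The concern.** Most of the gain from analysis of covariance usually comes from the outcome's own baseline. How much someone drinks on a drinking day and how often they drink are different dimensions of consumption, so baseline drinks per drinking day may predict 12-month days abstinent only weakly. If the named covariates are carried over unchanged to the second primary outcome, its interval is wider than the collected data allow, and the estimate keeps more of the random error that comes from chance imbalance in baseline abstinence.

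This matters because the Sample size and power calculation section says the trial is meant to yield an effect estimate with an 80% interval for sizing a definitive study, from about 35 participants per group. Leaving site and SADQ stratum out of the model also gives up whatever precision the stratified allocation could provide if those factors are prognostic.

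**Working it through.** **1. The plan's own figure.** Inputs from Sample size and power calculation: effect size 0.5, alpha 0.2, power 80%, 35 per group followed up. Taking alpha as two-sided (the section does not say), n per group = 2 × (1.2816 + 0.8416)² / 0.5² = 36.1, which rounds up to 37. Power at 35 per group = Φ(0.5 × √(35/2) − 1.2816) = Φ(2.092 − 1.282) = 79.1%. The stated 35 therefore reproduces closely. A one-sided alpha would need only 23 per group, so two-sided is the match. The calculation is an unadjusted two-group comparison and takes no credit for any baseline covariate.

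**2. Relative precision for percentage days abstinent.** The article gives no correlations, so these are assumptions, taken in absolute value:
- r, between baseline and 12-month percentage days abstinent: 0.4 to 0.6
- c, between baseline drinks per drinking day and baseline percentage days abstinent: 0.3 to 0.5
- baseline drinks per drinking day predicts 12-month abstinence only through baseline abstinence, so its correlation with the outcome is r × c
- age and gender are in both models and do not alter the comparison

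The residual variance, as a share of the outcome variance, is 1 − r² with the own baseline and 1 − (rc)² with baseline quantity.

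| r | c | 1 − r² | 1 − (rc)² | Variance ratio | SE ratio | SE reduction |
|---|---|---|---|---|---|---|
| 0.4 | 0.3 | 0.840 | 0.9856 | 0.852 | 0.923 | 7.7% |
| 0.4 | 0.5 | 0.840 | 0.9600 | 0.875 | 0.935 | 6.5% |
| 0.5 | 0.3 | 0.750 | 0.9775 | 0.767 | 0.876 | 12.4% |
| 0.5 | 0.5 | 0.750 | 0.9375 | 0.800 | 0.894 | 10.6% |
| 0.6 | 0.3 | 0.640 | 0.9676 | 0.661 | 0.813 | 18.7% |
| 0.6 | 0.5 | 0.640 | 0.9100 | 0.703 | 0.839 | 16.1% |

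The reduction in standard error is about 6 to 19%. In sample-size terms this is 1/0.875 = 1.14 to 1/0.661 = 1.51, that is, 14 to 51% more participants for the same precision.

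**3. In the trial's own units.** Take an own-baseline correlation of 0.5 and a correlation of 0.2 between baseline quantity and the outcome (c = 0.4), with 35 per group. The 80% interval half-width is 1.2816 × √(2/35) × √(1 − correlation²):
- baseline quantity: 0.3064 × √0.96 = 0.300 SD
- own baseline: 0.3064 × √0.75 = 0.265 SD

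Power at effect size 0.5 is 80.3% and 87.2% respectively. The variance ratio is 0.96/0.75 = 1.28.

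**4. Wider range, without the through-abstinence-only assumption.** With an own-baseline correlation of 0.3 to 0.7 and a baseline-quantity correlation with the outcome of 0 to 0.3, the variance with baseline quantity is 1.00 to 1.96 times that with the own baseline. It is 1.00 where both correlations are 0.3. Power is 79 to 82% with baseline quantity and 82 to 95% with the own baseline.

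**5. Stratification factors.** The article gives nothing from which to size this part. With about 70 participants followed up, the SADQ stratum uses one degree of freedom and site one fewer than the number of sites.

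**The case against.** The strongest objection is that the article does not fix the model. The words *such as* make the list illustrative, and nothing says that baseline drinks per drinking day replaces baseline abstinence for the second outcome. A journal article also commonly leaves the full covariate list to the analysis plan, which is not shown. This stands in part. A reader might infer that percentage days abstinent and the secondary scales are certain to be adjusted for the wrong baseline, and the text does not support that. For the secondaries, the rule of similar analysis most naturally means each scale with its own baseline, and the collection schedule fits that reading.

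Two further replies stand in full. Adjusting for a different baseline does not bias a randomised comparison; it costs only efficiency. And the sample size assumes no covariate gain, so even the less efficient model gives about the planned power.

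The percentages rest wholly on assumed correlations. If baseline quantity also predicts later abstinence directly, in the same direction, the loss shrinks.

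What the objection does not remove is that the article chose to name covariates, and the drinking covariate it named belongs to only one of two primary outcomes. Followed as written, the sentence gives the second primary outcome a covariate set that can be improved with data already in hand, and it leaves out the factors used to stratify the allocation.

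**Conclusion.** The point holds as a conditional loss of precision for one primary outcome, not as an error in the estimate. If percentage days abstinent is analysed with the named set, its treatment effect is unbiased but normally less precise than with its own baseline. Under the stated assumptions the own baseline would cut the standard error by about 6 to 19%; the gain is nil if the two baselines predict equally well. The omission of site and SADQ stratum from the named set is a further gap whose effect cannot be sized from the article.

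It would go too far to conclude that the trial is underpowered, that the comparison is biased, or that the secondary outcomes are mis-adjusted. This is a free improvement to a model that the article describes for only one of its primary outcomes.

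**What to change.** Replace the covariate sentence with a rule covering both primary outcomes and the continuous secondaries: each continuous outcome is adjusted for its own baseline value where one is measured, plus site, SADQ stratum, age and gender. Percentage days abstinent then takes baseline percentage days abstinent, drinks per drinking day takes baseline drinks per drinking day, and each secondary scale takes its own baseline score. STAR has no baseline and should be named as the exception. Put the description of the primary model in the plural so that it plainly applies to both outcomes. If the analysis plan already says this, it is enough to align the article's wording with it.

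The cost is wording only. Every covariate is already collected or known at randomisation, and the sample size does not change.

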## Methods/Design

### Overview

The Assertive Community Treatment for Alcohol Dependence (ACTAD) study is a two centre single blind randomised controlled trial of assertive outreach plus care as usual (CAU) compared with a CAU control condition for people with alcohol dependence. The primary analysis will be intention-to-treat.

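### The primary ANCOVA does not name the randomisation strata (site and SADQ) among its covariates; if they are left out, the 80% intervals may be somewhat conservative

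*Protocol article*

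**What the plan says.** Under Randomisation and blinding, the article states: "Randomisation is stratified by severity of alcohol dependence", with the SADQ cut at 30, and also by site. It does not say how allocation is restricted within the strata (blocks, minimisation or other).

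Under Statistical analysis, there are two primary outcomes at 12 months: mean drinks per drinking day and percentage of days abstinent. They are to be analysed by ANCOVA "adjusting for known confounding variables such as baseline mean drinks per drinking day, age and gender". Continuous secondary measures are handled similarly, and binary outcomes by logistic regression. On reporting: "Estimates and the 80% confidence intervals will be presented".

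The number of sites is not consistent. The Overview says the study "is a two centre single blind randomised controlled trial", whereas the Process evaluation section speaks of interviews across three sites.

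**The concern.** When allocation is balanced within strata that predict outcome, the difference between arms varies less from trial to trial than under simple randomisation. A model without the strata leaves their variance in the residual, so its standard error does not reflect that gain. The estimate is sound, but its reported uncertainty is too large.

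The rule for filling the list does not help. Factors balanced by stratified randomisation are not confounders, so a rule based on known confounding gives no reason to include them. They belong in the model because they shaped the allocation and may be prognostic.

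The article gives some reason to expect that they matter:

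- **Site.** Usual care depends on what is available locally (Control intervention). Intake routes differ between services (Participants and baseline recruitment). Differences between research sites are to be examined (Process evaluation). No named covariate stands in for site.
- **SADQ.** It was chosen as a stratifier. Baseline drinks per drinking day may absorb part of its effect. That is less assured for percentage of days abstinent, whose own baseline is not named.

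At stake is the width of the 80% intervals, which the Sample size section makes the basis for planning a definitive trial.

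**Working it through.** **1. The plan's own figure.** The inputs are a two-sided alpha of 0.2 (the sidedness is not stated; two-sided fits), power of 80% and an effect of 0.5 SD. The article says "a sample of 35 in each group followed-up at 12 months would allow us to detect an effect size of the order of 0.5". The normal formula gives 37 per group (one-sided: 23). At 35 per group, power is 79.1% (78.8% with the t distribution) and the detectable effect is (1.2816 + 0.8416) × √(2/35) = 0.508. The stated 35 is therefore reproduced within 2 patients. On attrition, "Allowing a loss to follow-up of 25% would suggest we require 45 in each group, a total of 90 participants"; 35/0.75 = 46.7, so 47 against the stated 45. The covariate question does not alter these figures. They do show that planned power has no slack.

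**2. Analytic limit.** Let R² be the share of the variance left after baseline drinking, age and gender that the strata explain. With perfect balance within strata and the strata omitted:

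- reported SE / true SE = 1/√(1 − R²)
- coverage of the 80% interval = 2Φ(1.2816/√(1 − R²)) − 1

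For example, at R² = 0.10 the ratio is 1/√0.90 = 1.054. Then 1.2816 × 1.054 = 1.351, and coverage is 82.3%.

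**3. Simulation closer to the plan.** There were 8,000 trials per setting, with 90 randomised, four strata, blocks of 4 (assumed) and 78% followed up (35/45 = 0.778). The ANCOVA contained baseline drinking, age and gender, with and without three stratum terms. The Monte Carlo error of a coverage figure is √(0.8 × 0.2/8000), about 0.45 points. Power is for 0.5 residual SD.

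| Assumed R² | Analytic SE ratio | Analytic coverage, strata omitted | Simulated mean SE / empirical SE, omitted | Simulated coverage, omitted | Simulated coverage, included | Power, omitted → included |
|---|---|---|---|---|---|---|
| 0 | 1.00 | 80.0% | 0.2441/0.2461 = 0.99 | 80.3% | 80.2% | 78.0% → 77.5% |
| 0.05 | 1.03 | 81.1% | 0.2442/0.2400 = 1.02 | 81.0% | 79.7% | 77.6% → 78.1% |
| 0.10 | 1.05 | 82.3% | 0.2445/0.2357 = 1.04 | 81.4% | 79.9% | 77.5% → 79.7% |
| 0.15 | 1.08 | 83.5% | not run | not run | not run | not run |
| 0.20 | 1.12 | 84.8% | 0.2443/0.2246 = 1.09 | 83.8% | 81.0% | 79.9% → 84.2% |
| 0.30 | 1.20 | 87.4% | 0.2445/0.2190 = 1.12 | 85.2% | 80.4% | 79.6% → 87.1% |

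The simulated shifts fall short of the analytic limit at R² of 0.10 and above, because incomplete blocks and loss to follow-up disturb the balance.

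**4. When nothing goes wrong.** At R² = 0 coverage is nominal. With simple randomisation and R² = 0.20 it is 79.9% with the strata omitted.

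**5. Overlap between SADQ and baseline drinking.** A further simulation assumed a correlation of 0.5 between the two and kept baseline drinking in the model. When the strata marginally explained 13.6%, 14.8%, 16.8% and 20.4% of outcome variance, coverage with the strata omitted was 80.1%, 80.1%, 81.1% and 82.6%. With site as the only direct effect (12.7%) it was 81.9%. The SE was 0-6% too large.

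**The case against.** The strongest objection is that the list is one of examples. 'Such as' does not exclude site and SADQ, the article condenses a fuller protocol, and a complete covariate list may stand in an analysis plan that is not shown. That much is right. A reader might infer that the plan leaves both factors out and that its intervals therefore have the wrong coverage; the article does not support this. What remains is that it states a rule for choosing covariates, and that rule gives no reason to include the factors that define the allocation.

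The consequence is also conditional. It needs strata that are prognostic after baseline drinking, and allocation balanced within strata. The article gives neither an R² nor a restriction method.

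A larger effect is tempting to claim. A simulation with exactly balanced strata and no other covariates gives coverage of about 82%, 84% and 87% when the strata explain 10%, 20% and 30% of outcome variance. That is not the planned model, which adjusts for baseline drinking.

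The direction is conservative, which is the less harmful error in an exploratory trial. Nor is the benefit of stratifying lost: the estimate keeps it, and only the reported standard error misses part of it.

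Finally, the standard-error argument does not carry over to logistic regression. There, adding prognostic covariates changes the conditional odds ratio and does not shrink its standard error. This objection stands and limits the fix.

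**Conclusion.** The point holds in conditional form. Site and SADQ shape the allocation and are not named in the model. Running the ANCOVA with the named covariates alone would be valid but conservative and less efficient, with no bias in the treatment estimate.

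For a residual R² up to 0.10-0.15, coverage of the 80% interval is about 80-83% (analytic ceiling 83.5% at 0.15). At 0.20-0.30 the simulations reach 84-85%; the analytic limit of 87.4% at 0.30 would need perfect balance. Type I error falls below 0.20 correspondingly. At R² = 0.10, including the strata raises simulated power by about 2 points; at 0.20, by about 4. If the strata explain nothing, including them costs about half a point.

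All of this rests on assumed R² values, blocks of 4 and four strata. The omission from the named list is certain; the size of its effect is not. The effect is probably small, and the change is worth making because it costs almost nothing.

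**What to change.** In Statistical analysis, replace the open list with a fixed one. The ANCOVA for both primary outcomes and for the continuous secondary outcomes should include site and SADQ (the stratum or the continuous score) as fixed covariates, with the baseline value of the outcome being analysed, age and gender. Describe these as design factors and prognostic covariates, not confounders. Where SADQ is itself the outcome, its baseline score already serves as the SADQ term.

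For logistic models, include the design factors for consistency with the randomisation, and limit the number of covariates if events are few.

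Reconcile the two centres in the Overview with the three sites in the Process evaluation, and say which unit was the stratifier. The two statements may be compatible if one centre runs more than one service, but the answer sets the number of site terms.

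The cost is a line or two of wording and no new data. SADQ stratum takes one degree of freedom and site takes one (two sites) or two (three sites), so two or three in all. With about 70 followed up and five terms already in the model (intercept, arm and three covariates), residual degrees of freedom go from 70 − 5 = 65 to 63 or 62.
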